**Plans for Dissemination and Communication of Study Results**

The results will be published in a relevant medical journal and will be presented at scientific meetings where possible

**Appendix 1: Codes used to identify glitazone exposure**

prodcode drugsubstancename

469 rosiglitazone maleate

548 pioglitazone hydrochloride

5227 rosiglitazone maleate

6855 metformin hydrochloride/rosiglitazone maleate

7325 metformin hydrochloride/rosiglitazone maleate

7375 metformin hydrochloride/rosiglitazone maleate

9662 rosiglitazone maleate

9699 pioglitazone hydrochloride

10051 pioglitazone hydrochloride

11601 metformin hydrochloride/rosiglitazone maleate

11604 metformin hydrochloride/rosiglitazone maleate

11609 metformin hydrochloride/rosiglitazone maleate

11610 metformin hydrochloride/rosiglitazone maleate

11717 metformin hydrochloride/rosiglitazone maleate

11737 metformin hydrochloride/rosiglitazone maleate

11760 metformin hydrochloride/rosiglitazone maleate

13628 troglitazone

14164 metformin hydrochloride/rosiglitazone maleate

15232 rosiglitazone maleate

17580 metformin hydrochloride/rosiglitazone maleate

18220 metformin/pioglitazone

19472 pioglitazone hydrochloride

20287 pioglitazone hydrochloride

20889 pioglitazone hydrochloride

30316 metformin/pioglitazone

31077 metformin/pioglitazone

37617 rosiglitazone maleate

**Appendix 2: Codes used to identify Parkinson’s Disease**

Parkinson’s disease with no identified cause

| medcode | readterm |
| --- | --- |
| 1691 | paralysis agitans |
| 4321 | parkinson's disease |
| 8956 | parkinsonism with orthostatic hypotension |
| 9509 | [x]dementia in parkinson's disease |
| 10718 | o/e - parkinsonian tremor |
| 14912 | parkinson's disease nos |
| 16860 | o/e - parkinson gait |
| 17004 | o/e - parkinson posture |
| 53655 | o/e -parkinson flexion posture |
| 59824 | o/e-festination-parkinson gait |
| 86062 | [x]parkinsonism in diseases classified elsewhere |
| 96860 | cerebral degeneration in parkinson's disease |

Parkinsonism with identified causes

| medcode | readterm |
| --- | --- |
| 19478 | drug induced parkinsonism |
| 24001 | secondary parkinsonism due to other external agents |
| 26181 | secondary parkinsonism, unspecified |
| 33544 | parkinsonism secondary to drugs |
| 51105 | postencephalitic parkinsonism |
| 52589 | syphilitic parkinsonism |
| 72879 | [x]secondary parkinsonism, unspecified |
| 97170 | [x]other secondary parkinsonism |
| 100128 | vascular parkinsonism |

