**Exposures, Outcomes and Covariates**

Exposure will be determined by prescribing records, using code lists for individual OADs. Code lists for GTZs can be found in Appendix 1. The index date for each patient will be their first prescribing event that qualifies them for study entry (e.g. first exposure to a GTZ)

The outcome for this study is the first recording of a PD diagnosis after the index date, as identified from clinical and referral records, using the Read code list in Appendix 2. PD due to known causes will be excluded based on the recording of codes presented in Appendix 2.

Covariates to be explored due to their possible association with PD and potential confounding nature will be:

- Smoking status determined using the additional clinical details file
- HRT use determined using prescribing records
- Head trauma as determined by Read code recording
- Age and sex will be accounted for through matching
- Calcium channel blocker use as determined by prescribing records: This exposure has been shown to reduce the incidence of PD (Becker et al, 2008).
- Diabetes itself has been shown to be possibly associated with PD (Wahlqvist et al, 2012). Length of time between diabetes diagnosis and index date, and HbA1c level at index date will be determined and explored for possible confounding properties. In addition, the effect of time updated HbA1c levels will be explored.
- Metformin has been suggested to also have a protective effect against PD (Wahlqvist et al, 2012). As a very commonly prescribed diabetes medication, this will be explored in detail as described below under “Statistical Analysis”.

Other covariates that have not been shown to be associated with PD will also be explored in case of possible confounding, and will include:

- Alcohol consumption
- Body mass index
- Calendar year

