**Limitations of the Study Design, Data Sources and Analytic Methods**

Diagnoses of PD in the CPRD have a positive predictive value of 90% (Becker et al, 2008) and so a small degree of misclassification amongst outcomes is expected. However, this is likely to be non-differential with respect to GTZ exposure and would be expected to bias results towards the null. In addition, missing cases of PD are likely to be rare in our study population, given that the prevalence of PD is low in the general population. Misclassification of the exposure is also likely to occur to some degree, with patients not being completely adherent to prescribed medicines. However, diabetes is a serious condition for which patients are likely to be motivated to take their medication, and substantial misclassification is not anticipated. Again, misclassification is unlikely to be differential with respect to PD status and so a dilution of any effect towards the null would be expected.

Whilst a small number of risk factors for PD are known and will be accounted for in the design and analysis (e.g. age, sex, smoking), it is not anticipated that these factors will be strongly associated with the choice to prescribe a GTZ, and so confounding is not expected to be strong in this study. Nonetheless, the analysis plan ensures potential confounding will be addressed, and in particular the separate and potentially additive effects of GTZs and metformin will be assessed.

Since the study is conducted entirely within the population with diabetes, the generalisability of results may be affected. However, it is unlikely that any pharmacological effect of GTZs relevant to PD would be limited to people with diabetes only.

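### The Parkinson's disease case list holds one code for parkinsonism in another disease and five examination signs, so the primary outcome is wider than its own definition

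*Protocol*

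**What the plan says.** The protocol section on exposures, outcomes and covariates states: "The outcome for this study is the first recording of a PD diagnosis after the index date". It identifies these records by the Read codes in Appendix 2 and adds: "PD due to known causes will be excluded based on the recording of codes presented in Appendix 2".

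Appendix 2 has two tables. The first, the case list, is headed Parkinson's "disease with no identified cause" and has 12 codes. Among them are:
- 86062, "x]parkinsonism in diseases classified elsewhere";
- five codes marked as findings on examination, such as "o/e - parkinsonian tremor" (10718), "o/e - parkinson gait" (16860) and "o/e - parkinson posture" (17004), together with 53655 and 59824, which also describe posture and gait.

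The second table, for identified causes, has nine codes. One is 97170, a residual code for other secondary parkinsonism.

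On accuracy, the limitations section says: "Diagnoses of PD in the CPRD have a positive predictive value of 90" per cent. It expects the resulting misclassification to be non-differential and to bias towards the null. The statistical analysis section adds a sensitivity analysis that also requires at least two prescriptions for an anti-Parkinson's drug. The primary analysis has no such requirement.

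**The concern.** The list that is meant to put the definition into practice departs from it in two ways.

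- **Cause.** Code 86062 places the parkinsonism within another disease, yet it sits in the table for no identified cause. The exclusion acts only through the other table, so a patient whose only relevant record is 86062 is counted and never excluded.
- **Diagnosis.** The five examination codes record a tremor, a gait or a posture. They name no cause, so they do not conflict with the heading on cause. They do conflict with an outcome defined as a recorded diagnosis. A patient with one such entry, and no known-cause code, is a primary case from that date.

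The study tests for a protective effect. Events that are not PD and do not respond to glitazones dilute the contrast and make a false null more likely. The power calculation treats all 144 exposed events as PD.

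**Working it through.** **1. Codes against definition.** Of the 12 codes in the case list, 1 names another disease as the setting and 5 are examination signs. So 6 of 12 are not, on their own wording, a diagnosis of PD without identified cause.

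**2. The protocol's power.** Inputs from the power section: 43,000 exposed patients, 144 exposed events, five unexposed per exposed patient. A two-sided 5% level is assumed, since none is stated. With exposed risk 144/43,000 = 0.335% and unexposed risk 0.335%/RR, a two-proportion calculation gives 99.0%, 92.0% and 71.8% for reductions of 30%, 25% and 20%. The protocol states 99%, 91% and 71%, so its figures reproduce, with no allowance for false cases.

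**3. Dilution.** Let f be the share of counted unexposed cases that are not PD, with the same absolute false-case rate in both groups. Then

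observed RR = 0.75 × (1 − f) + f.

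Hold the 144 recorded exposed events fixed and take equal follow-up, so that unexposed events are 5 × 144/RR = 720/RR. The Wald calculation is

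power = Φ(|ln RR|/SE − 1.96), with SE = √(1/144 + RR/720).

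| f | Observed RR | SE | abs(ln RR)/SE | Wald power | Two-proportion power |
|---|---|---|---|---|---|
| 0 | 0.750 | 0.0894 | 3.22 | 90% | 92% |
| 10% | 0.775 | 0.0896 | 2.85 | 81% | 84% |
| 20% | 0.800 | 0.0898 | 2.49 | 70% | 72% |
| 30% | 0.825 | 0.0899 | 2.14 | 57% | 58% |

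**4. What removing the false cases recovers.** The true cases left are 144 × 0.75(1 − f)/observed RR in the exposed and (720/observed RR)(1 − f) in the unexposed. The rate ratio is again 0.75, and SE = √(1/exposed + 1/unexposed).

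| f | Exposed | Unexposed | SE | Wald power | Gain over step 3 |
|---|---|---|---|---|---|
| 10% | 125 | 836 | 0.0958 | 85% | about 4 points |
| 20% | 108 | 720 | 0.1032 | 80% | about 10 points |
| 30% | 92 | 611 | 0.1120 | 73% | about 16 points |

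**5. Dependence on how f is defined.** If the share g refers to the 144 exposed events instead, observed RR = 1/[(1 − g)/0.75 + g]. For g = 10%, 20% and 30% this gives 0.769, 0.789 and 0.811, with Wald power of 83%, 75% and 65%. The direction is the same and the loss is smaller.

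**The case against.** The case on the other side has four parts.

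- **Only one code contradicts the heading; the signs are a trade-off between sensitivity and specificity.** In part this stands. The sign codes name no cause, and some patients coded this way will have PD. But the protocol chose a diagnosis as its outcome, and a sign entry is not one.
- **Misclassification is already handled.** The two-prescription analysis would filter out untreated patients who have only a sign code, and the limitations section discloses imperfect accuracy. Both help. But the sensitivity analysis states no change to the code list and leaves the primary result as it is. The predictive value is quoted for diagnoses, and nothing in the protocol extends it to signs.
- **The illustration is not specific to these codes.** This stands. A 10% false share equals the protocol's own predictive value of 90%, which would dilute the estimate even with diagnosis codes alone.
- **Cleaning the list costs events.** This stands too, and step 4 of the working allows for it.

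A reader might also count code 8956, parkinsonism with orthostatic hypotension, as a seventh wrong code. The protocol does not support that: the term names no other disease or cause, and treating it as a separate syndrome would rest on outside knowledge.

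**Conclusion.** The Appendix 2 case list conflicts with the protocol's outcome definition. This follows from the text alone and depends on no assumed figure. The bias is towards the null if the false cases are non-differential, which is the protocol's own expectation for outcome misclassification.

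The size is not known. Two stronger conclusions may tempt a reader, and the protocol supports neither:
- Six of 12 codes does not mean that half the events are false. There are no counts per code, the disputed codes may contribute few of the 144 events, and patients who also have a diagnosis code stay cases with at most a later date.
- Correcting the list would not bring power back to 90%. On the illustrative shares of 10%, 20% and 30%, the recoverable gain is about 4, 10 and 16 points. It is smaller if true cases known only by a sign are lost as well.

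These figures rest on an assumed false share, a true rate ratio of 0.75, no glitazone effect on false cases, equal follow-up and a two-sided 5% level. The change should be made, because the inconsistency is clear and cheap to remove.

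**What to change.** 1. Move 86062 to the identified-causes table.
2. In the primary analysis, require a PD diagnosis code and date the event at the first such code. Do not count the five examination codes as events on their own.
3. Keep the broad list for excluding patients with prior PD at entry, and repeat the analysis with it as a sensitivity analysis.
4. Recount the 144 events by code, report how many rest only on 86062 or a sign, and restate the power.

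The cost is an edit to the code list and a rerun of the feasibility count. The downside is fewer events, including some true cases known only by a sign code; the broad-list sensitivity analysis shows how much this matters.
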